### Analytical methods

Participants in the three conditions will be compared on demographic, smoking history and nicotine dependence characteristics to confirm successful randomisation. Participant outcomes will be analysed on an “intention to treat” basis [24], i.e. analysed in the condition to which they were randomly allocated regardless of whether they actually received any of the allocated intervention, subsequently withdrew from the study, or deviated from the protocol. Those lost to follow up will be modelled in various ways including having continued to smoke (the most conservative assumption). This approach gives pragmatic estimates of the benefit of a change in policy under various assumptions, rather than of potential benefit in participants who receive the intervention exactly as planned.

The primary outcomes will be analysed with multivariable logistic regression to determine the odds ratio for each outcome measure for Condition B and Condition C compared to Condition A and for Condition C compared to Condition B. Baseline characteristics (demographic, smoking history and quit intention variables) will be included as covariates to adjust for any baseline differences between the conditions. This will also reduce the impact of any differences between the sample composition and the Australian smoking population. Results will be reported as the odds ratio for quitting smoking and the odds ratio for quitting all nicotine use associated with each of the test policy scenarios compared to the relevant referent categories (Condition A or B).

Subsidiary analyses will explore quitting as a function of trying and of time to relapse, and assess whether relapse is related to cessation of medicinal nicotine/e-cigarettes. Percentages (e.g. percentage who quit) will be calculated with the data weighted to the Australian smoker population using a nationally representative sample (e.g., NDSHS [25]). Unweighted data will be used in the regression analyses.

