### Sample size

In a general population of Australian smokers, 34 % will make a quit attempt over a 7 month period [22]. We expect differential recruitment of those more interested in quitting, and participation in the trial to stimulate more quit attempts than in a natural setting. We assume that approximately 60 % of the sample will take up the products beyond the sample pack, with the proportion of these making a quit attempt similar to that observed in clinical trials. The 12 month abstinence rate in a systematic review of randomised controlled trials of medicinal nicotine for quitting was 12 % [15]. Therefore, we expect an abstinence rate of smokers in condition A of 60 % of 12 %, i.e. 7 %. A sample size of 1600 (N_A_ =340; N_B_ =630; N_C_ =630) will provide greater than 80 % power to detect a 5 % difference in abstinence rates at 12 months (1-tailed test, p < 0.05) between conditions A and B, A and C, and B and C. The unequal allocation between conditions maximises the statistical power for the total sample. Testing between conditions B and C will require a greater sample size than testing between conditions A and B (or A and C) because the difference in proportions to be tested is 12 % vs 17 % rather than 7 % vs 12 %.

A one-tailed test was chosen as the hypotheses are unidirectional because both new policies (Conditions B and C) are departures from the current abstinence only policy and would require a substantial change in current Australian policy. This pragmatic trial is only interested in outcomes in one direction; less conservative and more difficult to implement policies must produce significantly greater quitting than less difficult policies to be given further consideration. If they produce fewer quitters, the policy implications will be the same as if they produced equivalent or inferior results, with no change in *status quo* likely to be supported.

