### Primary outcomes

The primary outcome is the percentage in each condition that have:Continuous abstinence (not smoked for at least six months) with or without current/recent medicinal nicotine or e-cigarette use; andContinuous smoking abstinence forat least six months with no medicinal nicotine or e-cigarette use for 3 months or more.

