As the intervention is delivered without face-to-face contact with the participants, we selected an earlier generation e-cigarette as these require minimal instructions for use and represent very low risk because the nicotine liquid is contained within a sealed cartridge in the device rather than requiring participants to handle refilling fluids. Furthermore, research suggests that most smokers who switch to e-cigarettes start with a cigalike-style device, suggesting these may initially be more attractive and acceptable to smokers than larger tank style devices [26]. Due to Australian laws that prohibit the supply of nicotine as non-therapeutic products [16], we were restricted in what could be used as the trial product. We selected Vype e-cigarettes for the trial as they met our requirements for quality assurance over the manufacturing of the device and the liquid contained within it, which needs to be of medicinal quality. The e-cigarette market is rapidly evolving with constant improvements in the technology. Therefore, the product tested in this trial will not necessarily be representative of e-cigarettes in general or the most effective e-cigarette on the market in terms of nicotine delivery.

This study relies on self-report for assessing smoking abstinence and use of nicotine products. The majority of data is collected in online surveys delivered via a third party (I-View). Similarly, trial products are ordered via the study website and do not require interaction with the research team unless the participant requires assistance. A follow-up phone call is made early after participants are sent their ordered products to provide an opportunity to ask questions, however smoking outcomes are assessed via the online surveys. The risk of participants inaccurately reporting smoking abstinence due to social desirability bias is low due to the minimal direct contact the participants have with the research team. Because participants in all conditions received an intervention any tendency to please the researchers is likely to be equivalent across conditions. Participants also receive incentive payments for completing the surveys regardless of whether they quit smoking or not.

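### Counting those lost to follow-up as smokers is labelled the most conservative assumption; that holds for a quit percentage within one arm, not for the between-arm odds ratios of the primary analysis

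*Protocol article*

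**What the plan says.** Under Analytical methods, the protocol article analyses everyone in the allocated condition and adds: "Those lost to follow up will be modelled in various ways including having continued to smoke (the most conservative assumption"). The next sentence says what this is for: "This approach gives pragmatic estimates of the benefit of a change in policy under various assumptions". The benefit of a policy change is a difference between conditions.

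The primary outcome is defined per condition ("The primary outcome is the percentage in each condition that have" the stated abstinence). Its analysis is a multivariable logistic regression with three contrasts, B v A, C v A and C v B. The article gives its purpose as "to determine the odds ratio for each outcome measure for Condition B and Condition C compared to Condition A and for Condition C compared to" (the last reference being B).

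The Sample size section states: "A sample size of 1600 (N_A_ =340; N_B_ =630; N_C_ =630) will provide greater than 80 % power". The target of that calculation is given as "to detect a 5 % difference in abstinence rates at 12 months (1-tailed test, p < 0.05"). The section assumes abstinence of 7%, 12% and 17% in A, B and C and states no loss to follow-up. On data collection, the Discussion says: "The majority of data is collected in online surveys delivered via a third party".

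**The concern.** The label is attached to a method for estimating between-arm benefit, but the property it names belongs to a single-arm percentage. Setting every lost participant to smoking lowers the percentage in each arm by the quitters hidden among that arm's lost. If the arms lose different shares of their quitters, they are lowered by different amounts and the odds ratio moves.

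The tests are one-sided, so only an upward error can produce a claim of benefit. If more of the quitters in a new-policy arm are observed, the supposedly safest analysis can show a benefit that does not exist. If fewer are observed, it can hide a real one.

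Unequal response is possible on the article's own account. Participants know which products they are offered. Some contact depends on ordering: the ten-day call follows receipt of a sample pack, and the post-sampler survey accompanies an initiation-pack order. The Hypotheses section also considers that e-cigarettes may increase product use.

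**Working it through.** **The plan's own figure first.** One-sided 5%, pooled-variance normal test, no continuity correction: 7% v 12% with 340 v 630 gives power of 80.7%; 12% v 17% with 630 v 630 gives 81.0%. The stated figure of above 80% reproduces and is not in dispute.

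**Inputs.** From the article: arm sizes, one-sided 5%, and the 7% and 12% rates. Assumed, because the article gives none: response shares, abstinence among the lost, and a 10% common rate for illustration.

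**Formulas.** Let *p* be true abstinence in an arm, *r* the response share, and *k* abstinence among the lost divided by abstinence among responders. The responders' rate is p / [r + (1 − r)k]. With the lost counted as smokers, the analysed rate is

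q = r·p / [r + (1 − r)k].

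The odds ratio is [q₂/(1 − q₂)] / [q₁/(1 − q₁)]. The chance of a one-sided rejection is 1 − Φ{[1.645·SE₀ − (q₂ − q₁)] / SE₁}, where SE₀ is the pooled and SE₁ the unpooled standard error on all randomised.

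**One case in full.** A v C, p = 10% in both, response 60% v 75%, k = 1.
- q_A = 0.60 × 0.10 = 0.060; q_C = 0.75 × 0.10 = 0.075.
- OR = (0.075/0.925) / (0.060/0.940) = 1.27.
- Pooled rate = (340 × 0.060 + 630 × 0.075)/970 = 0.0697, so SE₀ = 0.0171; SE₁ = 0.0166.
- (1.645 × 0.01714 − 0.015)/0.01661 = 0.79, so the false-positive rate is about 21%.

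**Range, equal true rates, 340 v 630.**

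| True rate | Response, A v new arm | k (both arms) | Analysed rates | OR | False-positive rate |
|---|---|---|---|---|---|
| 10% | 60% v 75% | 1 | 6.0% v 7.5% | 1.27 | 21% |
| 10% | 60% v 75% | 0.5 | 7.5% v 8.6% | 1.16 | 14% |
| 10% | 60% v 70% | 1 | 6.0% v 7.0% | 1.18 | 14% |
| 10% | 60% v 70% | 0.5 | 7.5% v 8.2% | 1.11 | 10% |
| 10% | 75% v 60% | 1 | 7.5% v 6.0% | 0.79 | 0.7% |
| 7% | 60% v 75% | 1 | 4.2% v 5.25% | 1.26 | 17% |
| 7% | 60% v 65% | 1 | 4.2% v 4.55% | 1.09 | 8% |
| 10% | 60% v 75% | 0 | 10% v 10% | 1.00 | 5% |
| 10% | 70% v 70% | 1 | 7.0% v 7.0% | 1.00 | 5% |

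For B v C (630 v 630, true 12% in both, k = 1), response of 70% v 80% gives OR 1.16 and 18.4%; 80% v 70% gives OR 0.86 and 0.8%. At the planned 12% v 17% (true OR 1.50), 70% v 80% gives OR 1.72, while 80% v 70% gives OR 1.27 with power of 37%.

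**When *k* differs by arm (true 10% in both).**
- Response 60% with k = 0.5 v 75% with k = 1: both arms show 7.5%, so OR 1.00 despite unequal response.
- 60% with k = 0.25 v 75% with k = 0.75: 8.6% v 8.0%, which favours the arm that responds less.
- 70% in both, with k = 0.5 v 1: 0.07/0.85 = 8.2% v 7.0%, so OR 0.84 despite equal response.

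**A less favourable rule for C exists.** In the case worked in full, keep C's lost as smokers (7.5%) but credit A's lost with the responders' 10%: A becomes 0.060 + 0.40 × 0.10 = 10%. The odds ratio is (0.075/0.925)/(0.10/0.90) = 0.73, against 1.27 when all the lost are smokers. So counting all the lost as smokers is not the lower limit for the contrast.

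**The case against.** The strongest reply has four parts.

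- **The rule is only one of several.** The article promises estimates under various assumptions, so sensitivity analysis is already accepted in principle. This stands, and it makes the fix cheap, but the rule is still ranked as the safest of the set.
- **The design limits unequal response.** Participants do not know that other conditions receive a different offer. The market research company invites everyone to the surveys, including non-orderers, who get a dummy order date. The $30 card for each of the last two surveys does not depend on condition or on quitting. All this makes a large gap less likely, but it does not rule out differences in engagement.
- **Direction and size are not shown.** True: without response rates, deflation is as open as inflation, and a five-point gap at the 7% rate moves the error only to about 8%.
- **An analysis plan may name the primary missing-data assumption.** True. A reader might infer that the article is at fault for fixing none. It is a condensed protocol, it does fix the population, model and contrasts, and this choice is commonly left to the analysis plan, so that is no finding.

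Two other stronger readings also fail. A reader might infer that the rule always favours the arm that responds more, or that it will favour C. The arm-specific cases above refute the first, and nothing in the article establishes the second. A reader might also infer that the article says the rule cannot raise false positives. It makes no statement about type I error; the label only suggests safety.

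**Conclusion.** The label is wrong for the quantity it is applied to. It is correct for the percentage within one condition and not guaranteed for the B v A, C v A and C v B odds ratios. This is a property stated wrongly, not a detail left out.

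The bias needs some quitting among the lost, together with unequal response or different behaviour of the lost by arm. Under equal true rates there is none if response is equal and the lost behave alike in both arms, or if nobody lost has quit. For A against a new-policy arm, the cases with equal *k* in both arms put the one-sided false-positive rate anywhere from under 1% to about 21%, against a nominal 5%. The range rests wholly on assumed response and is not a forecast. The planned power figures are unaffected by this point.

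**What to change.** - Restrict the phrase to within-arm quit percentages, or delete it.
- Report survey response by condition beside the primary odds ratios.
- Include among the planned models (a) multiple imputation by condition, using baseline variables, earlier surveys and product-order records, and (b) a grid, fixed in advance, that lets the abstinence odds of the lost differ by condition. State whether a conclusion of benefit survives them.

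Counting the lost as smokers can stay as one of the analyses. The cost is a change of wording and a little more analysis on data the trial already collects. The downside for the investigators is that a benefit depending on unequal response would be shown to be fragile.

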#### Inclusion criteria

Smokers at least 18 years old, smoke five or more cigarettes per day, are willing to try nicotine products, have internet access, have the ability to read and understand English and are willing to complete online surveys over one year. These criteria are assessed during an online screening questionnaire as part of the initial enrolment process. There is no requirement that the person be planning to quit smoking.

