#### Exclusion criteria

Participants are excluded if they are pregnant, breastfeeding, or planning to become pregnant within 12 months, or if they suffer from any of the following conditions: Diabetes mellitus treated with insulin, severe allergies, poorly controlled asthma or other throat or airway disease, stomach ulcer, kidney or liver disease, adrenal gland tumour, overactive thyroid, poorly controlled high blood pressure, a mental health/psychiatric condition that is being treated with regular medication, or stroke, heart attack or severe angina in the previous 2 weeks. Exclusion criteria are assessed by self-report.

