#### Initiation pack

After they have sampled their selected products, they are invited to return to the study website to order one or two products to receive in an *initiation pack* which contains an amount of their selected product(s) that should last approximately two to three weeks. Participants are also allowed to order the *initiation pack* directly rather than first ordering a sample pack, if they already have a clear preference (e.g., from prior experience of using the products)*.* They have up to four months after ordering their *sample pack* to order product(s) for their *initiation pack*. This is to maximise the number likely to use the products, particularly since our recruitment strategy includes participants who have no stated interest in quitting.

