### Data collection

#### Baseline measures

Information collected from each participant includes demographics (date of birth, sex, geographic location, household composition, education); smoking history (age started smoking, nicotine dependence measured with Heaviness of Smoking Index [HSI; time to first cigarette, cigarettes per day] [23], urges to smoke); quit attempts (time since last quit attempt, duration of last attempt); intentions to quit (motivation to quit, current quit plans, perceived difficulty of quitting); prior nicotine product use (experience with medicinal nicotine, e-cigarettes, smokeless tobacco, non-cigarette smoked tobacco; intention to use nicotine products); knowledge of harms of nicotine and smoking (causes of harms from cigarettes and compared to medicinal nicotine, e-cigarettes, and smokeless tobacco); and overall health.

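### The stated covariate groups leave out prior nicotine product use, and dual use is reported without a baseline split, so the Condition C e-cigarette figure cannot tell new from pre-existing use

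*Protocol article*

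**What the plan says.** **Eligibility.** The Inclusion criteria admit "Smokers at least 18 years old, smoke five or more cigarettes per day, are willing to try nicotine products, have internet access", with English literacy and willingness to complete surveys. The Exclusion criteria cover pregnancy-related reasons ("Participants are excluded if they are pregnant, breastfeeding, or planning to become pregnant within 12 months") and a list of medical conditions. Neither section mentions current or past use of medicinal nicotine or e-cigarettes. The Initiation pack section expects some participants to know the products already: they may skip the sample pack "if they already have a clear preference (e.g., from prior experience of using the products".

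**Baseline data.** Baseline measures lists product use as its own group: "prior nicotine product use (experience with medicinal nicotine, e-cigarettes, smokeless tobacco, non-cigarette smoked tobacco; intention to use nicotine products". It is separate from "smoking history (age started smoking, nicotine dependence measured with Heaviness of Smoking Index" and from quit intentions. The Recruitment section places the baseline survey before randomisation.

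**Adjustment.** In Analytical methods, "Baseline characteristics (demographic, smoking history and quit intention variables) will be included as covariates" to allow for baseline differences between conditions. The balance check in the same section names demographics, smoking history and dependence. Product use appears in neither list.

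**Outcomes.** The second primary outcome is at least six months of smoking abstinence "with no medicinal nicotine or e-cigarette use for 3 months or more". Secondary outcomes define medicinal-nicotine dual use as a proportion in each condition and e-cigarette dual use as a proportion in Condition C alone. Neither refers to baseline status. Aim 3 asks whether the new policies turn would-be quitters into long-term dual users.

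**The concern.** There are two separate issues, and they need different remedies.

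1. **Covariates.** The second primary outcome contains a product-use component. Someone who has used these products before may be more or less likely than a naive participant to be free of them later. This is the baseline variable closest in content to that component, it is collected, and the stated groups do not include it.

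2. **Dual use.** Aim 3 concerns movement into dual use, but the planned measure is how many dual users there are at follow-up. For medicinal nicotine, each condition is measured, so randomisation balances pre-existing users in expectation. For e-cigarettes only Condition C is measured, so no comparator is available to net them out.

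At stake are some efficiency in the nicotine-free primary analysis and the interpretation of the e-cigarette harm figure, which readers concerned with policy are likely to examine closely.

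**Working it through.** **The plan's own figure, for reference.** The stated power is above 80% at one-sided 0.05 with 340/630/630. Using power = Φ[(Δ − 1.645·SE₀)/SE₁], with SE₀ from the pooled proportion and SE₁ from the separate proportions:
- A vs B, 7% vs 12%: SE₀ = 0.02041, SE₁ = 0.01895; (0.05 − 0.03357)/0.01895 = 0.867, power 80.7%.
- B vs C, 12% vs 17%: SE₀ = 0.01984, SE₁ = 0.01979; (0.05 − 0.03263)/0.01979 = 0.878, power 81.0%.

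The stated power reproduces, and nothing below changes it.

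**Step 1: how far chance could unbalance prior use.** Let q be the share of baseline users (assumed; the article gives none). The 95% range for the difference between A (340) and B or C (630) is ±1.96·√[q(1−q)(1/340 + 1/630)]:

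| q | 95% range, points |
|---|---|
| 5% | ±2.9 |
| 10% | ±4.0 |
| 20% | ±5.3 |
| 30% | ±6.0 |

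If nicotine-free abstinence differed by 5 points between baseline users and non-users (assumed), a 4.0-point imbalance would shift the comparison by 0.040 × 5 = 0.2 points, against a target difference of 5. The effect on the primary result is small.

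**Step 2: what the Condition C e-cigarette figure can identify.** Let q be dual users at entry, r the share of them still dual users at follow-up, and p the uptake among the rest. The reported proportion is q·r + (1−q)·p, and the pre-existing share of it is q·r divided by that sum. With p = 15% (assumed):

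| q | Reported, r = 0.8 | Pre-existing share, r = 0.8 | Pre-existing share, r = 0.5 |
|---|---|---|---|
| 1% | 0.80 + 14.85 = 15.65% | 5% | 3% |
| 2% | 1.60 + 14.70 = 16.30% | 10% | 6% |
| 5% | 4.00 + 14.25 = 18.25% | 22% | 15% |
| 10% | 8.00 + 13.50 = 21.50% | 37% | 27% |
| 20% | 16.00 + 12.00 = 28.00% | 57% | 45% |
| 30% | 24.00 + 10.50 = 34.50% | 70% | 59% |

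Read in the other direction, a reported 18.25% (r = 0.8) fits uptake of 18.25% if q = 0, 15% if q = 5%, (18.25 − 8)/0.9 = 11.4% if q = 10%, or (18.25 − 16)/0.8 = 2.8% if q = 20%. One unsplit proportion cannot distinguish these cases.

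**Step 3: the medicinal-nicotine comparison.** If persistence is the same in both conditions, the difference in follow-up dual use is (1−q)(p₂ − p₁). With p₁ = 10% and p₂ = 15% (assumed), it is 4.75, 4.5, 4.0 and 3.5 points at q = 5, 10, 20 and 30%. With r = 0.8 and 340 vs 630, one-sided power falls from 72% at q = 0 to 60, 51, 38 and 29%. Among baseline non-users only, it is 70, 68, 63 and 58%. These figures show why a split is informative. They do not show bias: the smaller difference is the correct all-randomised effect under those assumptions.

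**The case against.** **The covariate bracket may be loose shorthand.** This is a condensed article, and the balance check groups variables differently from the baseline list. Quit attempts, knowledge of harms and overall health are also unnamed. That is fair, and a fuller document may list more. Product use is singled out because it is the baseline counterpart of a primary-outcome component. If the authors meant to include it, the change is a clarification.

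**Randomisation already protects the comparisons.** This stands. A reader might infer that pre-existing product users bias the primary results or enter the trial as primary outcomes. The documents do not support either. Everyone smokes at least five cigarettes a day at entry, so nobody starts abstinent; prior use is balanced in expectation; and ordinary standard errors already allow for chance imbalance. The quoted covariate sentence also governs the primary models, not the dual-use proportions, so the two issues should not be run together.

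**Aim 3 is counterfactual.** A reader might infer that baseline dual users should be removed from Aim 3. That goes too far. Someone who was a dual user at entry, would have quit under current policy, and instead stays a dual user is exactly the harm Aim 3 describes. Excluding that person would hide it, so the non-user figure can only supplement the all-randomised one.

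**Baseline e-cigarette use may be rare.** The Background says no nicotine e-cigarettes are on the therapeutic goods register, and Discounted products says the study website is the only legal supplier. This makes the upper rows of the Step 2 table speculative for nicotine devices. It does not make the rate zero, and the baseline survey asks about e-cigarette experience.

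**Current use may not be recorded.** The baseline description refers to experience and prior use. This stands, and it limits how sharp the split can be.

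**Conclusion.** The point holds in limited form. The named covariate groups omit a pre-randomisation variable that plausibly predicts the nicotine-free primary outcome and dual use. The loss is some precision and some protection against chance imbalance, with no bias; on the assumptions in Step 1 it is about 0.2 points against a target of 5. Power and sample size are unaffected, and the eligibility criteria need no change.

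The stronger part concerns reporting. As defined, e-cigarette dual use in Condition C has neither a baseline reference nor a comparator, so it cannot be read as uptake during the trial. The size is unknown. With 15% uptake and 50% to 80% persistence, pre-existing users make up 3% to 5% of the count at 1% baseline dual use and 27% to 37% at 10%. All of these rates are assumptions. The dilution in Step 3 also requires equal persistence across conditions, meaning no policy effect on those already using both products, and the documents do not establish that.

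**What to change.** 1. In Analytical methods, add the baseline variables on experience with nicotine products to the named covariates, for both primary outcomes and for the between-condition comparison of medicinal-nicotine dual use.
2. Keep the all-randomised dual-use proportion as the main Aim 3 figure.
3. Beside it, report dual use split by baseline product use, in particular for e-cigarettes in Condition C. Use current use at baseline if the survey records it, otherwise ever versus never use, and state which applies.

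The split uses a variable fixed before randomisation, so comparisons within each subset remain randomised. Recruitment, sample size and follow-up do not change, and no new data are needed if the ever/never split is used. The costs are a few extra model terms and subsets that are smaller and less precise than the full conditions.
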